### Outcome measures

#### Reliability of examiner

The initial evaluations will be performed by an examiner who will be duly trained by a “gold standard” evaluator following an evaluation protocol. To confer greater reliability to the results, the examiner will be blinded to the allocation of the participants to the different groups. A second examiner will perform the re-evaluations following the treatment protocols and will also be blinded to the allocation of the participants. This examiner will also be duly trained following the evaluation protocol.

### Evaluations

Research Diagnostic Criteria for Temporomandibular Disorders (RDC/TMD): Potentially eligible patients will be diagnosed using the RDC/TMD, which consists of a clinical exam involving the palpation of the temporomandibular joints an analysis of the mandible with the aid of digital calipers to measure vertical and horizontal movements and a stethoscope to evaluate joint sounds. Symptoms such as headache, fatigue and difficulty when chewing, bruxism, psychological state, and parafunctional habits will then be investigated.Visual analog scale: This scale will be used for the assessment of pain and consists of a 10-cm line with 0 (absence of pain) printed at one end and 10 (debilitating pain) printed at the other end. The participants will be asked to mark a place on the line that represents their current pain intensity. The researcher will subsequently use a ruler to register the distance from zero to obtain a numeric representation of the pain level. These procedures will be performed before and after treatment.Maximum vertical mandibular movement: The volunteer will be instructed to open his/her mouth a wide as possible. Maximum vertical mandibular movement will be measured as the distance between the maxillary and mandibular central incisors determined with the aid of digital calipers. The volunteer will then be instructed to exert pressure on the mandibular teeth with the mouth open and move the mandible to the right and left for the determination of excursion (distance between upper and lower mid points). These procedures will be performed before and after treatment.

### Statistical analysis

The results will be tested for normality using the Kolmogorov–Smirnov test. Parametric data will be submitted to analysis of variance (ANOVA) with the Tukey–Kramer post hoc test. Non-parametric data will be submitted to Friedman’s test. The level of significance will be set to 5% (*p* < 0.05).

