### Sample composition

The sample size was calculated based on studies found in the literature using maximum vertical mandibular movement as the basis, with a standard deviation of 9.82, a 5% significance level (*p* < 0.05), and 80% test power. The sample was determined to be 80 individuals, who will be allocated to two groups.Step 1 – Recruitment for the selection of patients who will participate in the study. The patients will receive clarifications regarding the objectives and procedures and those who agree to participate voluntarily will sign a statement of informed consent.Step 2 – The selected patients will receive an envelope containing a card stipulating to which group they will be allocated. The patients will not be aware of the content of the envelope.

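### A Kolmogorov–Smirnov test on the results chooses between ANOVA and Friedman's test, so no single laser-versus-LED analysis is fixed in advance, and the two branches answer different questions

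*Protocol article*

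**What the plan says.** The Statistical analysis section of the protocol article sets a two-stage rule. First, "The results will be tested for normality using the Kolmogorov–Smirnov test". The outcome of that test then selects the analysis: "Parametric data will be submitted to analysis of variance (ANOVA) with the Tukey–Kramer post hoc test", whereas "Non-parametric data will be submitted to Friedman’s test". Significance is judged at 5%. The section does not say which version of the Kolmogorov–Smirnov test is meant or what it is applied to (arm, visit, pooled values, changes or residuals). Neither branch is named as the default.

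The two outcomes described under Evaluations are pain on a visual analog scale, "a 10-cm line with 0 (absence of pain) printed at one end", and maximum vertical mandibular movement. Each is measured twice, before and after treatment. On size, the Sample composition section states: "The sample was determined to be 80 individuals, who will be allocated to two groups". The Hypothesis section is a comparison of laser with LED.

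**The concern.** A trial comparing two arms needs one between-arm comparison per outcome that is settled before the data are seen. Here a preliminary significance test on the outcome data makes that choice.

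This raises two problems:

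- **Which branch is taken.** The Kolmogorov–Smirnov test has two forms in common use. The classical form assumes that the mean and SD are known. The Lilliefors form corrects for estimating them from the same sample. They use different critical values, so the same data can pass one and fail the other.
- **What the branch tests.** ANOVA can test whether the arms differ. Friedman's test ranks repeated measurements within each patient and, with two visits, asks only whether values changed.

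A post-treatment pain score bounded at zero, in a trial that expects pain to fall, may well be skewed. The question of which branch applies is therefore practical.

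**Working it through.** **Inputs.** From the documents: 80 patients in two groups, SD 9.82, 5% significance, 80% power (Sample composition); two visits and a 0–10 VAS (Evaluations). Assumed: 1:1 allocation (40 per arm), no dropout, two-sided testing, a before/after correlation of 0.5, and the outcome shapes listed below. The documents give no outcome distribution.

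**The plan's own figure.** The total of 80 cannot be reproduced because no target difference is stated. Solved backwards with 40 per arm:

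δ = (1.960 + 0.842) × 9.82 × √(2/40) = 6.15, in the unit of the SD.

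This neither confirms nor refutes the 80. It gives only a scale for the last step.

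**Step 1: the two versions at n = 40.** The statistic is D, the largest distance between the empirical distribution and a normal curve with the sample's own mean and SD. The 5% critical value is 0.210 for the classical test and 0.138 for the Lilliefors version (by simulation). For truly normal data, P(D > 0.210) is about 0.01%, against a nominal 5%.

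**Step 2: how often each version rejects normality at n = 40** (at least 20,000 samples per shape).

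| Assumed shape | Classical | Lilliefors |
|---|---|---|
| Normal | 0.01% | 5% |
| VAS, N(3, 2.5) cut at 0 and 10 | 0.05% | 13% |
| VAS, 10 × Beta(1.5, 4) | 0.6% | 31% |
| Gamma, skew 1.0 | 1.1% | 33% |
| VAS, N(2, 2.5) cut at 0 and 10 | 2.3% | 58% |
| Gamma, skew 1.4 | 4.6% | 59% |
| Lognormal, σ 0.5 | 7.0% | 61% |
| VAS, 10 × Beta(1, 4) | 4% | 64% |
| Exponential | 23% | 91% |
| VAS, N(1, 2) cut at 0 and 10 | 24% | 93% |
| VAS, 10 × Beta(0.5, 4) | 54% | 99% |
| VAS, 10 × Beta(0.3, 4) | 96% | 100% |

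The Lilliefors critical value is the lower one, so the versions choose different branches in a share of samples equal to the difference between the columns. For the six rows from Beta(1.5, 4) to Beta(1, 4), the mild to moderate skew, that share is about 30–60%. It is 69% for N(1, 2) cut at 0 and 10, and falls to 4% for Beta(0.3, 4). If all 80 values were pooled, N(1, 2) cut at 0 and 10 would be rejected in 90% against 99.96%, a disagreement of about 10%.

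**Step 3: what the branches test.** With two visits, Friedman's statistic is (2k − m)²/m on 1 degree of freedom, where m is the number of patients and k the number whose value rose. Group does not enter it. Take mouth opening, with an equal improvement of 8 in both arms:

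- SD of change = 9.82 × √(2 × (1 − 0.5)) = 9.82.
- P(rise) = Φ(8/9.82) = 0.792, so k is about 80 × 0.792 = 63.4.
- Statistic: about (126.8 − 80)²/80 = 27.4, against a critical value of 3.84.

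In 3,000 simulated trials with no group difference, pooled Friedman was significant in 100% and the ANOVA group-by-time test in about 6%. Running Friedman within each arm does not repair this. With an equal improvement of 4, exactly one arm was significant in 50% of trials, which could be misread as a group difference.

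**Step 4: what the proposed replacement delivers.** At a true difference of 6.2, 40 per arm and correlation 0.5, simulated power is about 90% for ANCOVA on the before-treatment value and 79% for a comparison of changes. The residual SD explains the gain: 9.82 × √(1 − 0.5²) = 8.50, against 9.82.

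**The case against.** The strongest reply is that a journal article need not state the Kolmogorov–Smirnov version or the unit tested, since an analysis plan that is not shown may fix both. That stands as far as it goes: the silence alone is no fault. The article does, however, state the rule that the test selects the analysis, and settling the version would still leave the choice to the outcome data.

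Several stronger readings are tempting but not supported:

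- **That the pre-test is always either inert or decided by the software.** It is not inert under strong skew, and under very strong floor effects the two versions agree. The document names no software; the dependence is on the version of the test. Where the classical version practically never rejects, ANOVA is in effect the analysis.
- **That a floored pain score is where the versions differ most.** Disagreement peaks at intermediate shapes and then vanishes.
- **That the test is run on raw values, cell by cell or outcome by outcome.** The text speaks only of the results.
- **That the pre-test inflates type I error.** When it was simulated with a two-group rank test substituted for Friedman's, type I error stayed at 4.8–5.3%. That substitute is not in the plan, so the figure does not describe the written rule, but it does show that pre-testing alone is not the source of serious error here.

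Friedman's test in a two-arm comparison can also fairly be called a separate fault. It is used here only to show what the selection can change. Replacing it with a between-group rank test would remove the worst consequence and still leave the estimand (mean difference or rank shift) to be picked after the data are seen.

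**Conclusion.** The point holds in this limited form: the stated rule leaves the laser-versus-LED analysis unfixed until the outcomes have been examined. At about 40 per arm, under mild to moderate skew, the classical version rejects in about 1–7% of samples and the Lilliefors version in about 31–64%. Under very strong floor effects this difference disappears. The consequence is large because one written branch can compare the arms and the other tests only change over time.

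The rejection rates rest on assumed shapes and 1:1 allocation. The 100% figure rests on an improvement of 8, SD 9.82 and correlation 0.5. That Friedman's test on two visits makes no between-arm comparison rests on none of these. No skewed scenario was built for mouth opening, and the documents give no distribution from which to build one.

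**What to change.** Delete the normality test as a decision rule. For the VAS and for maximum vertical mandibular movement, name one main analysis to be used whatever the distribution: the laser-minus-LED difference in post-treatment means, adjusted for the before-treatment value by ANCOVA, with its 95% CI. Check the residuals graphically. Add one between-group rank or bootstrap analysis, named in advance, as a sensitivity analysis that cannot replace the main one.

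The cost is one rewritten paragraph before the data are analysed. It needs no extra patients, visits or measurements, because the before-treatment values are already collected.

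### The planned ANOVA with Tukey–Kramer (or Friedman's test) is not tied to the laser-versus-LED contrast; its power runs from about 60% to 95% depending on how it is read, and ANCOVA on the collected baseline does at least as well on every reading

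*Protocol article*

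**What the plan says.** - **Design.** The Interventions section describes two active groups, laser and LED. The Abstract and the Hypothesis set the comparison between them as the question.
- **Measurement.** For both pain (visual analog scale) and mandibular movement, the Evaluations section says: "These procedures will be performed before and after treatment". Every patient therefore has a baseline and a post-treatment value.
- **Analysis.** Under Statistical analysis, after a Kolmogorov–Smirnov check: "Parametric data will be submitted to analysis of variance (ANOVA) with the Tukey–Kramer post hoc test". Data that fail the check go to Friedman's test. The type of ANOVA, its factors and the contrast for laser versus LED are not given, and no baseline covariate is named.
- **Sample size.** Sample composition bases the number on one endpoint, "using maximum vertical mandibular movement as the basis", "with a standard deviation of 9.82", 5% significance and 80% power. It concludes: "The sample was determined to be 80 individuals, who will be allocated to two groups".

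**The concern.** A post hoc procedure such as Tukey–Kramer has work to do only when more than two means are compared. With two arms it has none, unless the means are the four arm-by-time cells (laser before, laser after, LED before, LED after). Those give six pairwise contrasts. Only one of them, laser after versus LED after, is a randomized comparison of treatment effect, yet the 5% is shared over all six. The cell layout also invites the argument that one arm improved and the other did not, which is not a comparison of the arms.

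The alternative for non-normal data has a related defect. Friedman's test ranks readings within each patient, so it can detect change over time but does not compare laser with LED.

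At stake is whether the 80 patients deliver the stated 80% power for the question asked. It also matters that several analyses with quite different power remain open under one sentence.

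**Working it through.** **Inputs from the article (Sample composition, Evaluations):** SD 9.82; significance 5%; power 80%; N = 80 in two groups; two measurement times.

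**Assumptions, because the article does not state them:** 40 per arm; two-sided test; no dropout; 9.82 is the SD of a single reading, equal before and after; pre-post correlation ρ of 0.3, 0.5 or 0.7.

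**Step 1. The plan's own figure.** N = 80 cannot be reproduced, because no difference to detect is given. It can only be inverted:
- Standard error = 9.82 × √(2/40) = 2.196.
- Normal approximation: Δ = (1.960 + 0.842) × 2.196 = 6.15.
- t test: Δ = 0.634 × 9.82 = 6.23.

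By construction, an unadjusted two-arm comparison after treatment has 80% power at this Δ.

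**Step 2. Tukey–Kramer over two means.** The critical |t| with 78 df is 1.99, the same as the t test. Power stays at 80% and the procedure is redundant.

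**Step 3. Tukey–Kramer over four cells.**
- Studentized range quantile q(0.95; 4, 156) = 3.673, so critical |t| = 3.673/√2 = 2.60. With 78 df it is 2.63.
- Noncentrality at the t-test difference = 0.634/√(2/40) = 2.84.
- Power for laser after versus LED after = 59.5% (156 df) or 58.5% (78 df).

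The contrast and its standard error are those of Step 2. The loss comes only from the critical value.

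**Step 4. Group-by-time test and ANCOVA.** Both use power = Φ(2.802/f − 1.960), where 2.802 = 6.15/2.196 and f is the SD relative to a single reading:
- Group-by-time (equivalent to a change-score test): f = √(2(1 − ρ)).
- ANCOVA on baseline: f = √(1 − ρ²).

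| ρ | Two arms, after only | Tukey–Kramer, four cells | Group-by-time | ANCOVA |
|---|---|---|---|---|
| 0.3 | 80% | about 60% | 65.8% (f = 1.183) | 83.6% (f = 0.954) |
| 0.5 | 80% | about 60% | 80.0% (f = 1.000) | 89.9% (f = 0.866) |
| 0.7 | 80% | about 60% | 95.1% (f = 0.775) | 97.5% (f = 0.714) |

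The difference that ANCOVA detects with 80% power is 6.23 × f = 5.9, 5.4 and 4.4. At ρ = 0 ANCOVA equals the unadjusted comparison, 80%.

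**Step 5. If 9.82 is instead the SD of the change.** A single reading then has SD 9.82/√(2(1 − ρ)).
- The change-score test has 80% at every ρ.
- For ANCOVA, f relative to 9.82 is √((1 + ρ)/2) = 0.806, 0.866 and 0.922. Power is 93.5%, 89.9% and 86.0%.
- For the after-only comparison, f = 1/√(2(1 − ρ)) = 0.845, 1.000 and 1.291. Power is 91%, 80% and 58%.
- Four-cell Tukey–Kramer tests that same contrast against a higher critical value, so it is lower still.

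ANCOVA again has the highest power throughout.

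**The case against.** **The article does not say that baseline is ignored.** A reader might infer that the planned ANOVA discards each patient's baseline and that this is why power falls to 60%. The text supports neither step. The ANOVA type is not given. Naming Friedman's test, a within-patient method, as the alternative suggests that repeated measures may be meant, and the group-by-time term then does use baseline. The fall to about 60% comes wholly from the four-cell multiplicity adjustment, since a comparison that ignores baseline altogether keeps 80%. This objection stands, and the point is therefore stated conditionally.

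**The shortfall is not proven.** The 60% needs four cells, Tukey–Kramer as the decision rule rather than as a follow-up to the F test, and the post-treatment cell contrast as the result. On the other readings power is 80%, or reaches 80% or more once ρ is at least 0.5. The inputs in Sample composition are incomplete as well. This also stands: one cannot say that the plan fails to deliver 80%, only that the stated test is not tied to it.

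**Covariates and model details are commonly left to a full protocol or SAP.** True, and a missing covariate would not be a finding by itself. But the article does name its tests, and two named choices do not fit: a post hoc procedure with no role in a two-arm comparison, and a non-parametric test that does not compare the arms.

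**The change within each arm is also of interest.** The Objective and Expected results sections speak of effects of both therapies. Within-arm changes can be reported for that purpose. With two active groups and no untreated or sham arm, however, they cannot be separated from natural course, so they are descriptive.

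**Conclusion.** The concern holds in conditional form. The Statistical analysis section names tests without fixing the laser-versus-LED contrast and without adjusting for a baseline that is already collected. Power at the back-solved difference is about 60% for Tukey–Kramer over four cells, 80% for a plain post-treatment comparison, and about 66% to 95% for a group-by-time test with ρ from 0.3 to 0.7. ANCOVA gives about 84% to 97.5% over the same range and is at least as powerful as each alternative.

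The sizes rest on a difference of about 6.2 that the article does not state, a 1:1 split, a two-sided 5% test, assumed correlations, and 9.82 as the SD of a single reading. If 9.82 is the SD of change, the figures move (change-score 80%; ANCOVA about 93.5%, 90% and 86%) but ANCOVA still has the highest power. The Friedman point rests on none of these assumptions.

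It would go too far to conclude that the trial is underpowered as planned, or that its ANOVA certainly neglects baseline. The documents leave both open.

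**What to change.** Replace the ANOVA and Friedman sentences under Statistical analysis with wording such as:

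> Each outcome after treatment will be compared between laser and LED by ANCOVA with the baseline value of that outcome as covariate. The adjusted difference with its 95% CI is the basis for the between-arm conclusion. Within-arm changes will be described only. For clearly non-normal data, a rank-based ANCOVA with baseline as covariate will be used.

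Replacing only the ANOVA sentence would not be enough, because Friedman's test would remain as the rule for non-normal data.

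The cost is analysis wording only. Baseline values are already collected, and no patients, visits or measurements are added. What is given up is formal testing of within-arm changes. The article reports the trial as still recruiting, so the change should be recorded before outcome data are analyzed.

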**Methods:**

The aim of the proposed study is to compare the effects of two sources of photobiomodulation in individuals with TMD. A randomized, controlled, double-blind, clinical trial is proposed, which will involve 80 individuals aged 18–65 years allocated to either a laser group or light-emitting diode (LED) group submitted to 12 sessions of phototherapy. The Research Diagnostic Criteria for TMDs will be used to evaluate all participants. Pain will be measured using the visual analog scale and maximum vertical mandibular movement will be determined with the aid of digital calipers.

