### Hypothesis

Based on previous studies conducted by different research groups, the proposed study will test the hypothesis that photobiomodulation in the form of low intensity laser compared to LED decreases pain and improves temporomandibular joint function, thereby accelerating the return to activities of daily living.

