## Methods / design

### Study design

This protocol is presented in accordance with the 2013 SPIRIT (Standard Protocol Items: Recommendations for Interventional Trials) Statement (see Additional file 1 for the populated SPIRIT Checklist and Fig. 1 for the trial schedule of enrollment, interventions, and assessments in accordance with recommended SPIRIT figure), which was developed to provide guidance in the form of a checklist of recommended items to include in a clinical trial protocol to help improve its content and quality. A randomized, controlled, clinical trial will be conducted at the dentistry and physical therapy clinics of University Nove de Julho (Brazil) involving individuals with TMD distributed between two groups. This protocol study received approval from the Human Research Ethics Committee of University Nove de Julho (São Paulo, Brazil) under process number 1.706.160. All potential participants will receive clarifications regarding the objectives and procedures and those who agree to participate voluntarily will sign a statement of informed consent, as stipulated in Resolution 466/2012 of the Brazilian National Board of Health.

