**Fig. 1 Fig1:**
[figure not shown]
The SPIRIT Statement is important to detail the methodology, ensuring a high quality of clinical trial protocols

The patients will be randomly allocated to either the photobiomodulation or LED group using a set of opaque, sealed, numbered envelopes to ensure concealment. Each envelop will contain a card stipulating to which group the volunteer will be allocated. The participants will then be sent for evaluations (Fig. 2).

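### Non-normal outcomes are sent to Friedman's test, which compares before with after and never compares laser with LED

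*Protocol article*

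**What the plan says.** The Statistical analysis section sets a two-branch rule. First, "The results will be tested for normality using the Kolmogorov–Smirnov test". Outcomes that pass follow one branch: "Parametric data will be submitted to analysis of variance (ANOVA) with the Tukey–Kramer post hoc test". Outcomes that fail follow the other: "Non-parametric data will be submitted to Friedman’s test". That is the only non-parametric method named.

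Other sections fix the design and the question:

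- Study design describes a randomised trial "involving individuals with TMD distributed between two groups", and the allocation text adds that "The patients will be randomly allocated to either the photobiomodulation or LED group". No crossover and no matching of patients is described.
- Evaluations gives two measurement times for both pain (VAS) and mandibular movement: "These procedures will be performed before and after treatment".
- The abstract states a comparison between the devices: "The aim of the proposed study is to compare the effects of two sources of photobiomodulation in individuals with TMD". The Hypothesis section is also comparative: "photobiomodulation in the form of low intensity laser compared to LED decreases pain and improves temporomandibular joint function".

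**The concern.** The randomised comparison is between patients, and Friedman's test works within blocks of related measurements. If it cannot carry a laser-versus-LED contrast, then a preliminary normality test decides whether the trial's hypothesis is tested at all for a given outcome.

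Pain is the outcome that looks most exposed. It is recorded on a line bounded at 0 and 10, and the Expected results section anticipates a fall in pain, which can pile post-treatment scores up near zero.

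Two errors could follow. A significant result might be read as evidence about the devices when it shows only that scores changed over time. A real difference between devices might go undetected because nothing tests for it.

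**Working it through.** **Step 1: what Friedman's test can be applied to.** The test needs blocks in which every level of the compared factor is observed. Each patient receives one device, so device cannot vary within a patient. Blocks containing one laser and one LED patient would require matched pairs, and none are planned. The only factor observed at all its levels within a patient is time, with k = 2 levels.

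**Step 2: the statistic at k = 2.** Let n+ and n− be the numbers of patients whose value rose and fell. Ignoring ties, the statistic is (n+ − n−)² / (n+ + n−), referred to chi-square on 1 degree of freedom. This is the sign test. Treatment arm does not appear in it. This result is structural and uses no assumed number.

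**Step 3: inputs for the size of the problem.**

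- From the Sample composition section: N = 80, SD 9.82, 5% significance.
- Assumed: 40 per arm, unit mm, two-sided testing, bivariate normal values, and pre-post correlation ρ of 0.5 (0.7 as an alternative).
- The article states no target difference, so the sample size cannot be reproduced. Inverting it gives 9.82 × (1.960 + 0.842) × √(2/40) ≈ 6.15. The arm difference used below, 2 × 3.115 = 6.23, is close to this.

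With 80 patients, significance requires (n+ − n−)² / 80 > 3.84, so |n+ − n−| ≥ 18, that is n+ ≥ 49 or n+ ≤ 31.

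**Step 4: no difference between devices, both arms improve by 5 mm.** The SD of change is 9.82 × √(2(1 − 0.5)) = 9.82. The chance that a patient's value rises is Φ(5/9.82) = 0.695. For a binomial count with 80 patients and p = 0.695, P(n+ ≥ 49) = 0.955. At ρ = 0.7 the SD of change is 7.61, p = 0.745, and the probability is 0.997. Simulation gave 96.1% and 99.7%.

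**Step 5: a real difference of 6.23 mm, arms changing by +3.115 and −3.115 mm.** At ρ = 0.5 the chance of a rise is Φ(±3.115/9.82), which is 0.625 in one arm and 0.375 in the other. The expected n+ is 40, exactly the null value, and the rejection probability is 4.9% (4.4% at ρ = 0.7). On the same data at ρ = 0.5:

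- A rank-sum test on change rejected in 78% of simulated trials.
- For ANCOVA the residual SD is 9.82 × √(1 − 0.25) = 8.50, so power ≈ Φ(6.23 / (8.50 × √(2/40)) − 1.96) = 0.91. Simulation gave about 90%.

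**Step 6: skewed data, the kind that would reach this branch.** Simulation of 5,000 trials per scenario, 40 per arm, log-normal outcomes, correlation 0.5 on the log scale. Changes are in SD units on the log scale.

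| Change, laser / LED | Pooled Friedman significant | Rank-sum on change significant |
|---|---|---|
| −0.4 / −0.4 | 82% | 4.7% |
| −0.5 / −0.5 | 94% | 4.7% |
| −1.0 / −1.0 | 100% | 4.3% |
| −1.6 / −0.95 | 100% | 43% |
| −0.325 / +0.325 | 5% | 77% |

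The third and fourth rows show the problem: Friedman gives the same answer whether the arms are equal or differ.

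**Step 7: Friedman run separately in each arm.** With equal improvement of 0.4 to 0.5 SD in both arms, one arm was significant and the other was not in 45% to 50% of these trials. Comparing two within-arm p-values does not replace a between-arm test.

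**The case against.** The strongest reply is that the defect is conditional and its size is overstated.

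- **Only outcomes that fail the normality test are affected.** This is right. ANOVA in the other branch can carry a group or group-by-time term. Nothing in the article shows that mandibular movement, on which the sample was sized, is non-normal, and no VAS distribution is given. The finding is limited to outcomes sent to Friedman's test.
- **The calculations in steps 4 and 5 use normal data, which would seldom reach Friedman.** This is fair, but the skewed data in step 6 show the same pattern, and step 2 depends on no distribution.
- **Opposite changes are contrived, since improvement is expected in both arms.** This also stands: step 5 isolates the flaw and is not a forecast. With the same 6.23 mm difference but gains of 6.23 and 0, the calculation of step 4 (ρ = 0.5) gives about 60% rejection, and with gains of about 8.1 and 1.9 it gives about 94%. Those rejections still reflect overall change and not the arm contrast. The equal-improvement case is the realistic one, and there the test misleads.
- **Friedman's test serves the Objective section, which asks about the effect of each therapy.** It can describe change within an arm. The abstract's aim and the Hypothesis are comparative, and for non-normal outcomes no named test addresses them.
- **An analysis plan not shown might add a between-group test.** It might, but the article names a specific test for this branch. That is a stated choice and not a detail left open.

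**Conclusion.** The concern holds. For any outcome that fails the normality test, the only method named contains no laser-versus-LED contrast. That conclusion follows from the design and needs no numerical assumption.

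The percentages rest on an assumed 1:1 split, unit, distribution and pre-post correlation. Under those settings Friedman's test is significant in 82% to 100% of trials when both arms improve equally (5 mm, or 0.4 to 1.0 SD), and in about 5% when a real arm difference cancels in the pooled data. This must be corrected before analysis, because pain, one of the two outcomes named in the abstract, could otherwise end with no test of the hypothesis.

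**What to change.** Remove the Kolmogorov–Smirnov gate and Friedman's test. Analyse every outcome by ANCOVA of the post-treatment value on arm and baseline value, and report the laser-minus-LED difference with its 95% confidence interval. For skewed outcomes such as VAS pain, state one sensitivity analysis in advance: a Wilcoxon rank-sum test on change from baseline with the Hodges–Lehmann difference, or rank ANCOVA.

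The minimum repair is to replace Friedman's test with a between-group method. Removing the gate as well has the advantage that the data no longer choose the test.

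The cost is about two sentences of analysis wording, and the planned before and after measurements are enough. The article reports that recruitment is under way, so the change should be recorded as a dated amendment before unblinding.
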